#### Secondary Outcomes

(1) Anthropometric parameters: body weight, waist circumference, hip circumference, BMI.(2) Physiological indicators: blood pressure, grip, vital capacity, maximum oxygen.(3) Biochemical indicators: blood lipid, blood sugar, liver enzyme, creatinine, and blood urea nitrogen.

#### Adverse Events

All adverse events reported during the study will be recorded on the case report form (CRF). In this trial, adverse events will be defined as any unfavorable and unexpected signs, symptoms, or diseases related to the intervention, such as falls, fractures, dizziness, high blood pressure, palpitations, chest pain, and low blood sugar. Researchers will ask the subjects about the adverse events they have experienced before the start of the training and record all the adverse events of the intervention. Participants will receive calls every week and ask about any adverse events experienced. Subjects will also be required to self-report any adverse events throughout the study protocol. A serious adverse event (SAE) will be notified to the lead investigator within 24 hours. The chief researcher is responsible for managing the safety report. Any adverse events related to the intervention will be reported to the ethics review committee of the Shanghai Institute of Physical Education. Although the committee and the author are from the same institution, the members of the ethics committee are independent of the investigators. None of these investigators are members of the ethics committee.

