#### Moderate-Intensity Exercise Group

Participants in moderate-intensity exercise group will be intervened at Shanghai University of Sport at 64-76% of maximum heart rate (220 - age) (17). The exercise frequency will be 30 minutes a day, 5 days a week, for a period of 12 months. The subject will wear a heart rate monitor during exercise to monitor exercise intensity. In the first 2-4 weeks, subjects will exercise for 15-30 minutes at 57-63% of their maximum heart rate. Then, the exercise intensity of the subjects will gradually increase to 64-76% of the maximum heart rate, and the time will be increased to 30 minutes. In addition, the moderate -intensity exercise group will maintain the same health education and prohibition of high-purine diet as the control group.

In the low-intensity exercise group and the moderate-intensity exercise group, all exercise sessions will be supervised by research staff. The exercise intensity, duration, heart rate and blood pressure before and after exercise, and adverse events during exercise will be recorded by study staff. The study participant retention is critically important and every effort will be made to increase participants’ adherence to their intervention and follow-up visit schedule. If the subject fails to participate in the study more than 3 times in a row, the researcher will call the subject to ask the reason and encourage the subject to continue participating in the study. During the research process, the researchers will also send personalized gifts to the participants to strengthen their enthusiasm.

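### The adverse event definition requires events to be both unexpected and intervention-related, which conflicts with the rest of its section and would make exercise-versus-control harms unlike for like

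*Protocol article*

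**What the plan says.** The only definition of an adverse event is in the Adverse Events section of the protocol article: "adverse events will be defined as any unfavorable and unexpected signs, symptoms, or diseases related to the intervention". Examples follow: "such as falls, fractures, dizziness, high blood pressure, palpitations, chest pain, and low blood sugar".

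The same section describes collection and reporting:

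- **Recording:** "All adverse events reported during the study will be recorded on the case report form".
- **Enquiry linked to training:** staff ask participants "before the start of the training and record all the adverse events of the intervention".
- **Weekly enquiry, not limited by arm:** "Participants will receive calls every week and ask about any adverse events experienced". Self-report is also required throughout the study.
- **Onward reporting:** "Any adverse events related to the intervention will be reported to the ethics review committee".

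Table 1 (Outcome Assessment) ticks adverse events at baseline and at months 3, 6 and 12, with no restriction by arm. The Moderate-Intensity Exercise Group section adds, for both exercise arms, that "adverse events during exercise will be recorded by study staff". The Control Group section describes health education, a ban on high-purine diets and otherwise unchanged habits, with no trial exercise.

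**The concern.** A definition decides what gets written down. This one sets two conditions before an unfavourable event counts: it must be unexpected, and it must be related to the intervention. Both are judgements about an event, and a harms comparison normally needs the event recorded first and judged afterwards.

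The relatedness condition does not act equally across arms. A fall or an episode of dizziness in someone jogging five days a week can plausibly be attributed to the intervention. The same event in someone attending monthly lectures rarely can. The control count would therefore be low because of the definition, whatever the true rate.

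The error can also run the other way, because an exercise-arm event put down as expected or unrelated would drop out.

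The trial is meant to inform physical activity guidance in hyperuricemia (Discussion), so it matters that harms are counted the same way in each arm.

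**Working it through.** The plan states no adverse event rate or safety figure, so there is nothing to reproduce. The check is textual, followed by an illustration under stated assumptions.

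**Passages side by side**

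1. *Definition against its examples.* The definition requires the event to be unexpected. Falls, dizziness and palpitations are foreseeable with exercise. If the word unexpected is applied, listed events fall out; if the list is applied, the word does nothing. Staff cannot follow both.
2. *Definition against collection.* The weekly calls, self-report, case report form entry and Table 1 cover all participants. Each collects adverse events, the term that has just been narrowed. Either the wide collection is meant and the definition is wrong, or the definition is meant and most of what control participants mention on the phone would not qualify.
3. *Definition against ethics reporting.* The committee receives adverse events that are related to the intervention. If every adverse event is related by definition, that qualifier is redundant. The sentence makes sense only if unrelated adverse events also exist.
4. *Training-linked enquiry and session recording.* The first is tied to training and to events of the intervention. The second happens at supervised sessions, which only the exercise arms have.

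The section is therefore inconsistent with itself, not restrictive throughout. No wider definition appears elsewhere in the article.

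**Illustration of the literal reading**

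Inputs:

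- n = 62 per arm (Sample Size Calculation section).
- p, the true risk of an event, the same in every arm: 10% to 30% (assumed).
- r, the share of exercise-arm events judged related: 25% to 100% (assumed).
- c, the share of control events judged related: 0 (assumed, the extreme case).

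The true risk difference is p − p = 0.

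Counted events per exercise arm = n × p × r, and in control = n × p × c. Apparent risk difference = p × (r − c).

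| p | r | c | Counted, exercise arm | Counted, control | Apparent difference |
|---|---|---|---|---|---|
| 0.10 | 0.25 | 0 | 62 × 0.10 × 0.25 = 1.6 | 0 | 2.5 points |
| 0.20 | 0.50 | 0 | 62 × 0.20 × 0.50 = 6.2 | 0 | 10 points |
| 0.30 | 1.00 | 0 | 62 × 0.30 × 1.00 = 18.6 | 0 | 30 points |
| 0.20 | 0.50 | 0.25 | 6.2 | 62 × 0.20 × 0.25 = 3.1 | 5 points |

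The last row relaxes the zero in control: the distortion shrinks, and it vanishes only when c = r. The table shows direction and mechanism. It does not predict the trial's data.

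**The case against.** The strongest reply is that the definition is one loosely worded sentence and the procedures around it are sound. All participants are called weekly, all must self-report, Table 1 has no arm restriction, and the control group's education and diet ban themselves appear under the Intervention heading. The ethics-reporting sentence implies that unrelated events are recorded as well. Chest pain is among the listed examples, and serious events have their own 24-hour route to the lead investigator. Adverse events are not among the primary or secondary outcomes, and the Mathematical Statistics section describes no safety comparison.

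Much of this stands, and it rules out four stronger readings that a reader might infer:

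- *That control-arm events are expressly removed.* They are not. Few would meet the definition as worded, but no text excludes the arm.
- *That safety cannot be compared at all.* Low and moderate intensity share the same session schedule and calls and remain largely comparable. The collection procedures would support the exercise-versus-control comparison too, once the definition is corrected.
- *That staff who know the allocation judge causality.* The article does not say who judges relatedness or expectedness, or what that person knows. Session staff record events, which is not the same as assessing their cause.
- *That unequal contact measures the bias.* Scheduled contacts are 5 × 52 = 260 sessions plus 52 calls, 312 in all, against 52 calls in control, a ratio of 6. This assumes full attendance and counts contacts, not events. One weekly call can cover the whole preceding week, so the ratio says nothing about the effect of the definition.

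The reply does not remove the defect. The definition is stated, so it is not a detail left to a fuller document. Wide collection of a narrowly defined term still leaves staff to decide which rule governs.

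**Conclusion.** The concern holds in a limited form. Taken literally, the definition excludes expected and unrelated events and makes few control-arm events eligible, so exercise-versus-control harms would not be compared like for like. It also contradicts its own examples, the collection from all participants and the ethics-reporting sentence.

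The size cannot be determined from the document. The illustrative range of 2.5 to 30 points rests on assumed event risks, assumed attribution shares and no related events in control. If staff in practice record everything that participants report, the distortion could be small. The wording should be corrected, but it does not invalidate the trial, and the efficacy outcomes are unaffected.

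**What to change.** 1. Define an adverse event as any untoward medical occurrence after randomisation, in any arm, whatever its cause and whether or not it was expected.
2. Record relatedness, expectedness and seriousness as separate fields on the case report form.
3. Reconcile the sentences of the Adverse Events section with that definition: the examples, the training-linked enquiry, and the ethics-reporting sentence, which then correctly names a subset.
4. Base any between-arm comparison on events elicited by the identical weekly call. List events observed at sessions separately, as a description of the exercise arms.

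The cost is a change of wording, some added form fields and somewhat more events to record; the weekly calls are already planned. The change should be made before events are collected, because an event never recorded cannot be recovered. The Trial Status section places the trial before recruitment when the article was submitted.

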#### Mathematical Statistics

The data collected in the experiment will be statistically analyzed by SPSS 25.0, and the results will be expressed in the form of mean ± standard deviation. According to the specific values of each index, the Kolmogorov-Sminov test is used to determine whether it conforms to the normal distribution. If the index conforms to the normal distribution, the independent sample T-test is used to judge the difference between the two groups, and the paired sample T-test is used to judge the difference between each group before and after the intervention. If the index does not conform to the normal distribution, the Mann-Whitney test in the non-parametric test is used to judge the difference between the two groups, and the Wilcoxon test is used to judge the difference before and after the intervention in each group. Spearman correlation analysis is used to test the correlation of each index. P= 0-0.05 is set as the significance level.

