**Methods and Analysis:**

A randomized, single-blind, parallel controlled trial will be conducted in this study. 186 HUA patients who meet the inclusion criteria will be randomly divided into a 1:1:1 ratio (1): control group (2), low-intensity exercise group (brisk walking, 57-63% maximum heart rate, 150 min/week, 12 months), and (3) moderate-intensity exercise group (jogging, 64-76% maximum heart rate, 150 min/week, 12 months). The three groups of subjects will receive the same health education and prohibition of high-purine diet during the intervention period. The primary outcomes will be SUA concentration, SUA concentration change (mg/dL), SUA change rate (%), and the proportion of HUA patients. Secondary outcomes will include anthropometric parameters (body weight, waist circumference, hip circumference, BMI); physiological indicators (blood pressure, grip, vital capacity, maximum oxygen); biochemical indicators (blood lipid, blood sugar, liver enzyme, creatinine, and blood urea nitrogen). Each group of patients will go through an assessment at baseline, 3rd, 6th, and 12th months.

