### Inclusion Criteria

(1) Men and women;(2) Age: 45-60 years old;(3) Diagnose with HUA, within 4 weeks. Under normal purine diet, two fasting tests on different days, SUA>7mg/dL (male), SUA>6mg/dL(female);(4) No history of gout;(5) Agree and sign the informed consent form.

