#### Primary Outcomes

The concentration of SUA, the amount of concentration change (mg/dL), the rate of change (%), and the proportion of patients with SUA concentration ≤7.0 mg/dL (male) or ≤6.0 mg/dL (female) from baseline to the 3rd, 6th, and 12th months will be observed. Detection method: The blood samples will be collected between 8:00 am and 10:00 am. Subjects should keep fasting for 12 hours, that is, eating and drinking after 8 o’clock the day before blood collection is prohibited. Each subject will collect 5 mL of blood. The blood sample will be centrifuged at 3500r/min for 15min. The obtained serum samples will be stored in a refrigerator at -80°C and tested by Zhongshan Hospital with Fudan University.

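### A yes/no primary outcome (SUA at or below 7.0/6.0 mg/dL) has only a continuous-data analysis rule, and its before-after test within each arm cannot serve as evidence of an exercise effect.

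*Protocol article*

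**What the plan says.** The Primary Outcomes section lists SUA concentration, its change, its rate of change, and a responder-type outcome: "the proportion of patients with SUA concentration ≤7.0 mg/dL (male) or ≤6.0 mg/dL (female) from baseline to the 3rd, 6th, and 12th months". The abstract names the complement, "SUA change rate (%), and the proportion of HUA patients".

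Mathematical Statistics gives one rule for the data collected and makes no exception by type of variable. For description, "the results will be expressed in the form of mean ± standard deviation". A Kolmogorov-Smirnov check then chooses the tests. If an index is normal, "the independent sample T-test is used to judge the difference between the two groups", with a paired t-test within each group. If it is not, Mann-Whitney is used between groups and "the Wilcoxon test is used to judge the difference before and after the intervention in each group". No summary, test or model for a proportion is named.

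The Inclusion Criteria require "two fasting tests on different days, SUA>7mg/dL (male), SUA>6mg/dL(female", with timing given as "Diagnose with HUA, within 4 weeks". These cut-offs are the exact complement of the outcome threshold. Table 1 lists serum uric acid at baseline but does not say whether that value is one of the qualifying tests or a new sample. The abstract and the Intervention section give all three arms the same health education and high-purine diet ban.

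**The concern.** There are two problems of different weight.

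1. **The rule does not fit the variable.** A 0/1 outcome cannot be normal, so the rule as written leads to Mann-Whitney and Wilcoxon, with mean ± SD as the summary. For a 0/1 variable the SD is fixed by the proportion and adds nothing, and a rank test produces a P value without an effect size or interval. A primary outcome should have an interpretable between-arm estimate.

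2. **The before-after test on this outcome does not isolate exercise.** Education and the diet ban can move patients below the threshold in any arm, including control. Eligibility is also defined on the same threshold. If a qualifying value is carried forward as baseline, every patient starts above it. Ordinary within-person variation can then produce only apparent improvement, because no one can cross in the other direction.

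The risk is that a report presents a significant within-arm rise in the proportion at target as a benefit of exercise. The Discussion section's first expected result is a decrease under low-intensity exercise with no comparator named, so this use is not remote.

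**Working it through.** **Inputs from the article.** The outcome and eligibility cut-offs are 7 and 6 mg/dL. The sample size is 53 per group (159 in total), with 62 recruited, and α = 0.05. The 159 is reproduced by a three-group F test at power 0.80 if Cohen's f = 0.25 (power 0.805); f is not stated, and nothing below depends on it except the use of n = 53.

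**Step 1: between arms.** On 0/1 data the Mann-Whitney z equals the Pearson z times sqrt((N-1)/N). With two arms of 53, N = 106 and the factor is sqrt(105/106) = 0.995. In no-effect simulations it rejected in at most about 5.8% of comparisons. The test is valid; what is missing is the estimate with its interval.

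**Step 2: before-after, if baseline is 0%.** Let m patients cross and none cross back. The m non-zero differences are equal, so each has rank (m+1)/2. The positive rank sum exceeds its null mean by m(m+1)/4, and its null SD is sqrt(m)(m+1)/4. Hence z = sqrt(m).

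| m of 53 | Wilcoxon P (asymptotic) | paired t P | exact P (McNemar) |
|---|---|---|---|
| 3 (5.7%) | 0.083 | 0.083 | 0.25 |
| 4 (7.5%) | 0.046 | 0.044 | 0.125 |
| 6 (11.3%) | 0.014 | 0.013 | 0.031 |

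Four crossers are enough with the asymptotic test and six with an exact one. An exact within-arm test therefore has the same one-way problem at a slightly higher count.

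**Step 3: how often an unchanged patient crosses.** The article gives no SUA distribution and no within-person SD, so these are assumptions: true SUA normal with mean 6.5-7.0 and SD 1.0-1.2 mg/dL, within-person SD 0.4-0.6 mg/dL, and entry on two readings above 7 (male threshold only). Let q(T) be the chance that one reading exceeds 7 given true level T. With no true change, P(later reading ≤ 7) = E[q²(1-q)] / E[q²]. The chance that a no-effect arm of 53 is declared improved is P(Binomial(53, p) ≥ 4).

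| mean, SD, within-person SD | p crossing | arm declared improved |
|---|---|---|
| 7.0, 1.2, 0.4 (lowest on grid) | 8.4% | 66% |
| 7.0, 1.0, 0.5 | 12.9% | 92% |
| 6.5, 1.0, 0.6 (highest on grid) | 21.0% | 99.8% |
| 7.5, 1.2, 0.3 (off grid) | 4.4% | 20% |
| 8.0, 1.0, 0.3 (off grid) | 3.0% | 7% |

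Over a wider set (means 6.0-8.5, SD 1.0-1.2, within-person SD 0.2-0.7) the last column runs from 0.2% to 100%.

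**Step 4: before-after, if baseline is a fresh measurement.** On the Step 3 grid, 8-21% of patients already read at or below 7 at baseline. With no effect, crossings in the two directions are then equally likely. The asymptotic Wilcoxon rejects in about 4.3-4.8% of no-effect arms, roughly 2% of them towards improvement. The inflation disappears.

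**The case against.** **The baseline may be a separate sample.** Table 1 lists SUA as a baseline assessment. The blinding section says SUA values are hidden from the investigator and patient, which sits awkwardly with using a value that must be known in order to enrol. This stands. A reader might infer that the baseline proportion is about 0% and that the before-after test will show improvement even with no effect. The article does not support that as a fact: it never says a qualifying value is the baseline, and Step 4 shows nominal size if it is not. Pointers the other way (no separate screening column in Table 1; diagnosis and blood tests at the same hospital) make reuse plausible, no more.

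**The size rests on chosen inputs.** This also stands. Step 3 can be moved from near 0% to near 100% by inputs that the article does not give.

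**The statistics section may be meant only for continuous measurements, with the proportion left to a fuller plan.** This stands in part. The section never names the proportion, and test detail is often left to an analysis plan. But the rule is stated for the data collected without exception, and it does not fit a listed primary outcome.

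**The between-arm result is not uninterpretable.** This is correct. The mean of a 0/1 variable is the proportion, so a risk difference can be recovered from the arm means. Only its confidence interval, or an adjusted estimate, is unplanned.

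**The abstract's hypothesis is stated against control, so within-arm tests do not carry it.** This is true of the hypothesis. The statistics section nevertheless plans the within-arm tests and gives them no lesser role.

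**Conclusion.** The point holds in a limited form. The stated analysis rule does not suit the threshold outcome: the between-arm test is acceptable, but no risk difference or odds ratio with a confidence interval is planned. The before-after test of this outcome should not be read as evidence for exercise under either reading of baseline, because the education and diet ban act in every arm.

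False improvement in the absence of any change is a conditional risk. It requires that a qualifying value serves as baseline; then 4 of 53 crossers suffice (asymptotic P = 0.046). Its frequency is 66% to over 99% under one assumed set of SUA inputs and 7-20% under others. With a fresh baseline it is about nominal.

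This should be corrected, since a primary outcome is affected. It does not undermine the trial: SUA concentration remains analysable, and the between-arm comparison of proportions remains valid.

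**What to change.** In Mathematical Statistics, add a rule for the threshold outcome:

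- Report n/N (%) per arm at each visit in place of mean ± SD.
- Compare the randomised arms with a logistic or risk-difference model adjusted for baseline SUA and sex, and give the odds ratio or risk difference with a 95% CI. A chi-square test with n/N (%) would close the descriptive gap but would not use baseline SUA.
- Do not use the before-after test of this outcome as evidence of effect. Replacing Wilcoxon with McNemar does not cure the problem.
- State which measurement is the baseline: a qualifying test or a new sample.

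The cost is a few sentences of wording and one standard model. No new data are needed.

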### Intervention

#### Control Group

The subjects in the control group will be given health education and maintain their original lifestyle. Control subjects will be given a monthly uric acid popular science lecture, such as the relationship between hyperuricemia and gout, diet control of hyperuricemia patients, and correction of poor lifestyles. During the study period, high-purine diets will be banned.

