## Discussion

Studies have shown that the improvement of SUA level helps reduce the risk of chronic disease, such as hypertension (28, 29), obesity (30), diabetes (31–33), insulin resistance (34, 35).

Several small clinical trials have evaluated the effect of short-term physical exercise on SUA in HUA patients. Shu Yuan and his colleagues reported that the SUA of a 45-day aerobic exercise program (1600-meter jogging) decreased by 10.5% (P <0.05) (27) This is consistent with the findings of J Strength Cond Res et al. They reported that patients with mild to moderate high blood pressure in men with 60-79% maximum heart rate reserve for 8 weeks of aerobic exercise, SUA reduced by 41.8% (P <0.05) (36). However, another study showed that 12 weeks of strength training increased the SUA of patients with type 2 diabetes (P <0.001) (37). The study by Li-Ling Huang et al. (20) showed that the SUA level of professional athletes was significantly increased after short-term high-intensity training (P <0.05). The mechanism may be reduced uric acid excretion after high-intensity exercise, which in turn leads to an increase in SUA. Therefore, low and medium exercise may be a suitable choice to improve HUA.

This study is a randomized, multi-center, parallel trial, which aims to explore the impact of low- and moderate-intensity exercise on HUA. The expected results of this study are (1): Low-intensity exercise (brisk walking for 150 min a week, 57-63% maximum heart rate) would have a significant decrease in SUA at 6 and 12 months for HUA patients (2). Compared with the control group and the low-intensity exercise group, the moderate-intensity exercise group (jogging for 150 min a week, 64-76% maximum heart rate) would have a greater reduction in SUA levels at 6 months and 12 months (3); Low-intensity exercise and moderate-intensity exercise can significantly improve body weight, waist circumference, fat composition, blood sugar, liver function, and other chronic diseases. These results can provide a basis for the current physical activity guidelines for HUA’s healthy lifestyle management.

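### Before-after tests within each arm carry the same 0.05 level as between-arm tests, and one expected efficacy result names no comparator, although all arms share a diet change

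*Protocol article*

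**What the plan says.** For normally distributed indices, the Mathematical Statistics section of the protocol article plans a between-group comparison, "the independent sample T-test is used to judge the difference between the two groups", and also a within-group one, "the paired sample T-test is used to judge the difference between each group before and after the intervention". For other indices it plans Mann-Whitney between groups, and within groups "the Wilcoxon test is used to judge the difference before and after the intervention in each group". One threshold covers everything: "P= 0-0.05 is set as the significance level". The section does not say which family of tests decides efficacy.

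The Discussion lists three expected results. The first is that low-intensity exercise "would have a significant decrease in SUA at 6 and 12 months for HUA patients"; no comparator is named. The second compares moderate intensity with control and with low intensity. The third, on weight, waist, blood sugar, liver function and similar indices, again has no comparator. The hypothesis in the Abstract is stated against no-exercise control; the one at the end of the Background is not.

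Eligibility rests on "two fasting tests on different days, SUA>7mg/dL (male), SUA>6mg/dL(female"), measured "Under normal purine diet". After entry, the Control Group section states: "During the study period, high-purine diets will be banned". The two exercise arms receive the same ban and the same health education.

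**The concern.** Everyone's diet is meant to change between eligibility testing and follow-up, and everyone is educated about uric acid. A before-after fall in an exercise arm mixes any effect of exercise with that shared change and with time trends, and possibly with regression to the mean. A paired test cannot separate these; only the randomised comparison can.

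Two wrong conclusions become possible. Low-intensity exercise could be called effective on a fall of the same size as in control. And if one arm reaches significance while another does not, the contrast could be read as an intensity effect although the two falls do not differ. The Discussion says the results may inform physical activity guidelines, so the distinction matters outside the trial.

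**Working it through.** **Inputs from the article.** Evaluable patients 53 per arm (159 in total) and α = 0.05, from Sample Size Calculation. Two-sided testing is assumed because sidedness is not stated.

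**The plan's own figure.** The effect size f behind the G*Power F test is not given. With f = 0.25 assumed, three groups, α = 0.05 and power 0.80, the noncentral F distribution gives N = 159 (power 0.805), which matches. For 15% loss, 159/0.85 = 187.1, against 186 stated; that is close and plays no part here. So n = 53 per arm is used below.

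**Inputs not in the article (assumed).** Fall from diet and education common to all arms, δ = 0.2 to 0.4 mg/dL; SD of within-person change, s = 0.7 to 1.3 mg/dL; exercise effect zero.

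**Step 1: chance that a paired t-test is significant in an arm with no exercise effect.** The noncentrality is δ√n/s with 52 degrees of freedom and critical value 2.007. For δ = 0.3 and s = 1.0 it is 0.3 × 7.280/1.0 = 2.184, which gives 57%.

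| Shared fall (mg/dL) | s = 0.7 | s = 1.0 | s = 1.3 |
|---|---|---|---|
| 0.2 | 53% | 30% | 20% |
| 0.3 | 87% | 57% | 38% |
| 0.4 | 98% | 82% | 59% |

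At δ = 0.3 and s = 0.8 the figure is 76%.

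**Step 2: two arms with the same true fall.** If each is significant with probability p, exactly one of the two is significant with probability 2p(1 − p). For δ = 0.3:
- s = 0.8: 2 × 0.764 × 0.236 = 36%
- s = 1.0: 2 × 0.573 × 0.427 = 49%

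**Step 3: between-arm test under the same conditions.** A fall common to both arms cancels in the difference. In simulation with no exercise effect, the two-sample test was significant in 4% to 6% of trials in every scenario, against a nominal 5%.

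**Step 4: regression to the mean.** This depends on whether the baseline SUA is one of the two qualifying readings or a new sample, which the article does not say. Patients were simulated with two readings above 7.0 mg/dL and no treatment.
- *A qualifying reading serves as baseline.* With population mean 5.8 to 6.2, SD 1.2 to 1.3 and reliability 0.75 to 0.85 (all assumed), the mean fall is about 0.14 to 0.30 mg/dL, and the paired test is significant in 32% to 73% of arms. Wider assumptions (mean 5.5 to 6.0, SD 1.2, within-person correlation 0.6 to 0.9) give 0.10 to 0.56 mg/dL and 28% to 99%.
- *Fresh baseline sample.* The mean fall is zero, with significant falls in 2% to 3% of arms. Only the diet and education route in Step 1 remains.

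**The case against.** The strongest reply is that the randomised comparison is already planned and listed first, that the Abstract's hypothesis names the control group, and that the second expected result is explicitly between-arm. The first expected result is a forecast in a Discussion, not a decision rule, and a statistical analysis plan that is not shown may say which test is confirmatory. This stands as a limit on severity. It does not remove the point, because the article itself fixes the within-arm tests at the same level and itself words an efficacy expectation that such a test alone could satisfy.

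The size of the shared fall is also assumed. Controls are told to keep their original lifestyle apart from the ban, and the limitations paragraph says purine intake is not strictly controlled, so the diet effect could be small. At 0.2 mg/dL with SD 1.0 to 1.3, a significant fall occurs in only 20% to 30% of arms. That stands too: a significant fall in control is possible, not assured.

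Three stronger readings are tempting and not supported:
- A reader might use the Background's 10% to 18% reduction to size the diet effect. That figure is for a package that includes regular exercise and weight control, so it cannot.
- A reader might treat regression to the mean as certain. It needs a qualifying reading to serve as baseline, and no section says that it does.
- A reader might infer that the proportion at or below the cut-off starts at 0% and so can only improve, giving a before-after significance rate of 88% to 99.9%. This needs the same unstated premise. With a fresh baseline, 16% to 28% are already at or below 7.0 mg/dL and no net change follows. The article also names no before-after test for a proportion.

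**Conclusion.** The point holds in a limited form and should be fixed. Within-arm tests stand beside between-arm tests at the same level with no stated priority, and the first expected result can be met without reference to control. A significant paired test would not show that exercise works in this design, because all arms share a planned diet change and education. The error risk is about 20% to 98% per arm under the assumed falls and SDs. A split result between two identical arms occurs in 36% to 49% of trials at a 0.3 mg/dL shared fall with SD 0.8 to 1.0. The between-arm test keeps its error near 5%. Regression to the mean would add to the problem only if a qualifying reading is the baseline; the conclusion does not rest on it.

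The documents do not support saying that within-arm tests are half of the inference, or that the trial has no valid efficacy test: the between-arm tests are there. What is missing is the statement that they alone decide.

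**What to change.** - In Mathematical Statistics, label the paired t and Wilcoxon results as descriptive only. They need not be deleted.
- In the same section, state that every efficacy conclusion rests on between-arm differences reported with 95% confidence intervals.
- In the Discussion, reword the first expected result as low-intensity exercise versus control at the 6 and 12 months already named there, and add the control comparator to the third.

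The cost is a few sentences, with no new data and no change to the sample size. The Trial Status section says the trial was still preparing for recruitment when the article was submitted, so on that timing the change could be made before outcome data existed.
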